## Abstract

**Background:**

Persecutory delusions are strong threat beliefs about others’ negative intentions. They can have a major impact on patients’ day-to-day life. The Feeling Safe Programme is a new translational cognitive-behaviour therapy that helps patients modify threat beliefs and relearn safety by targeting key psychological causal factors. A different intervention approach, with growing international interest, is peer counselling to facilitate personal recovery. Combining these two approaches is a potential avenue to maximize patient outcomes. This combination of two different treatments will be tested as the Feeling Safe-NL Programme, which aims to promote psychological wellbeing. We will test whether Feeling Safe-NL is more effective and more cost-effective in improving mental wellbeing and reducing persecutory delusions than the current guideline intervention of formulation-based CBT for psychosis (CBTp).

**Methods:**

A single-blind parallel-group randomized controlled trial for 190 out-patients who experience persecutory delusions and low mental wellbeing. Patients will be randomized (1:1) to Feeling Safe-NL (Feeling Safe and peer counselling) or to formulation-based CBTp, both provided over a period of 6 months. Participants in both conditions are offered the possibility to self-monitor their recovery process. Blinded assessments will be conducted at 0, 6 (post-treatment), 12, and 18 months. The primary outcome is mental wellbeing. The overall effect over time (baseline to 18-month follow-up) and the effects at each timepoint will be determined. Secondary outcomes include the severity of the persecutory delusion, general paranoid ideation, patient-chosen therapy outcomes, and activity. Service use data and quality of life data will be collected for the health-economic evaluation.

**Discussion:**

The Feeling Safe-NL Trial is the first to evaluate a treatment for people with persecutory delusions, while using mental wellbeing as the primary outcome. It will also provide the first evaluation of the combination of a peer counselling intervention and a CBT-based program for recovery from persecutory delusions.

**Trial registration:**

Current Controlled Trials ISRCTN25766661 (retrospectively registered 7 July 2022).

## Administrative information

Note: the numbers in curly brackets in this protocol refer to SPIRIT checklist item numbers. The order of the items has been modified to group similar items (see http://www.equator-network.org/reporting-guidelines/spirit-2013-statement-defining-standard-protocol-items-for-clinical-trials/).

## Introduction

### Background and rationale {6a}

Persecutory delusions are strong threat beliefs with specific content about others’ negative intentions. They are common and transdiagnostic experiences in people with severe mental health problems [1], and they are associated with impairments in multiple functional domains. About half of patients with persistent persecutory delusions experience psychological wellbeing scores in the lowest 2% of the general population [2]. Considering the impact of persecutory delusions on patients' daily life, it is crucial that they receive treatment. Effective treatments include medication and formulation-based cognitive behaviour therapy for psychosis (CBTp) [3, 4]. Yet the effect sizes for those two treatments are small to moderate and treatment outcomes can be improved [3].

The new translational Feeling Safe Programme, a targeted psychological treatment addressing key contributory causal factors, has demonstrated large treatment effects for persecutory delusions (*d* = 1.2 when compared to an active psychological control condition), the largest treatment effects for persecutory delusions to date [5]. Besides advances in psychological therapy, there is an internationally growing trend to adopt peer counselling in mental healthcare [6, 7] with evidence for positive effects on personal recovery [8, 9]. Both clinical and personal recovery independently and synergistically contribute to improved mental wellbeing [10]. Uniquely bringing together these two promising approaches, Feeling Safe and peer counselling — two different types of interventions, delivered by different staff members at the same time and in collaboration, has the potential to maximize patients’ recovery and mental wellbeing. This combination will be called ‘The Feeling Safe-NL Programme’ and our aim is to provide an evaluation against the psychological guideline intervention of formulation-based CBTp.

#### The Feeling Safe Programme

Research has shown that there are several common empirical maintenance factors of inaccurate threat beliefs that patients frequently wish to be treated [11]. The Feeling Safe Programme is the culmination of over a decade of research and involves a translational approach in which five psychological maintenance factors of threat beliefs (worry, low self-esteem, anomalous experiences, insomnia, and safety-seeking behaviours or defences) are identified and addressed with CBT modules of approximately six to eight sessions [5]. These brief CBT modules have been specifically adapted for patients with persecutory delusions and have been tested in separate randomized controlled trials. Therapy modules include: improving sleep [12], increasing self-confidence [13], reducing worry [14], reducing the impact of voices, and feeling safe enough [15]. The Feeling Safe Programme is an individual therapy of approximately 20 sessions in which on average three therapy modules are completed, including the core module focused on rediscovering safety by reducing safety-seeking behaviours or defences and building experiences of being safe enough [5]. For each person it is first determined which of the maintenance factors are contributing to sustaining their fear of others. This results in a personalized treatment menu. The therapist consults, but the patient decides what modules to do and in what order, giving the patient control from the outset. As a result, brief CBT modules are delivered that match the persons’ experiences and personal choice: e.g. ‘I want to sleep better’ or ‘I want to worry less’. The strategy is to address maintenance factors one-by-one, then enter previously avoided situations to enable the person to learn they are safe enough. Through helping people to re-engage with activities while gradually lowering their defences people build new memories of being safe enough. The overarching goals are to feel safer, happier, and get people back to doing what they want to do. These goals and the overall program were positively evaluated by patients [16] and resulted in large effect size improvements in persecutory beliefs and wider benefits including improvements in mental wellbeing and participation in day-to-day activities [5].

#### Peer counselling

Recovery from severe mental health problems is a complex and personal process and peer counselling is referred to as the help and support of people with lived experience of mental health problems to navigate this process [6]. The foundation of peer counselling is that people who have faced, endured and overcome adversity can offer hope, emotional support and experiential knowledge (i.e. knowledge gained through experience) to facilitate recovery [17]. Peer-counselling is one of the roles of experts by experience, which refers to people who are able to share learning in different contexts based on their experiential knowledge. Peer counsellors can promote people’s recovery in mental healthcare settings through reciprocal sharing of experiences, identifying meaning in past and current experiences, and by promoting experiential knowledge through helping people to reflect on their experiences and strengths. Peer counsellors are increasingly involved in delivering mental healthcare [6, 7], and in The Netherlands, peer counsellors have a professional register, code and competence profile [18, 19]. A recent review on the effectiveness of peer counselling reported small positive effects on clinical recovery, overall personal recovery and more specifically hope, in particular for people with severe mental illness [8]. Qualitative research also reveals the instalment of hope as a recurring theme, alongside other themes including reciprocal sharing of experiences, both contributing to the central concept of de-stigmatization [20]. For one-to-one peer support, specifically, psychosocial benefits have been found including improvements in self-reported recovery and empowerment [9]. Also in an experimental setting, research has shown a benefit of delivering recovery-oriented messages by peers [21]. Postulated mechanisms of peer support include sharing of lived experience, emotional engagement, the liminal position between mental healthcare staff and patients, strengths-focus and reducing internal stigma [22]. Some of these unique aspects of peer counselling are promising for promoting recovery and mental wellbeing in patients with persecutory delusions.

#### The Feeling Safe-NL Programme

The combination of Feeling Safe and peer counselling moves towards a dual approach to therapy. Therapists work on reducing the maintenance factors of inaccurate threat beliefs (persecutory delusions) using brief CBT modules and supporting patients to relearn safety. At the same time, professional peer counsellors focus on addressing personal recovery by sharing of experiences, identifying meaning in past and current experiences, and helping people to build experiential knowledge. Besides the close collaboration between therapists and peer counsellors, Feeling Safe-NL offers a trauma-imagery module based on the evidence for trauma imagery as a treatable psychological causal factor of threat beliefs [23, 24]. The trauma imagery module replaces the reasoning biases module, as this module was rarely chosen and the reasoning biases factor is also implicitly addressed in other therapy modules [5]. Additionally, the program offers people the possibility to self-monitor change during their recovery process since this has been found to promote shared decision-making, agency [25] and motivation [26]. Together, the Feeling Safe-NL Programme provides a clear framework for tackling complex problems: install hope and build experiential knowledge while reducing the maintenance factors of persecutory delusions one-by-one, then with support re-enter situations, directly re-learn safety and work towards personal recovery goals.

#### The Feeling Safe-NL Trial

This randomized controlled trial will recruit outpatients with persecutory delusions, independent of the Diagnostic and Statistical Manual of Mental Disorders (DSM)-classification. The primary hypothesis is that the Feeling Safe-NL Programme will lead to greater improvement in mental wellbeing over time (from baseline to 18-month follow-up) than formulation-based CBTp. The secondary hypotheses are that the Feeling Safe-NL Programme will be more effective than formulation-based CBTp over time (from baseline to 18-month follow-up) in 1) reducing the severity of the persecutory delusion, 2) reducing general paranoid ideation, 3) improving patient-chosen outcomes of therapy and 4) improving activity levels. We also hypothesize that the Feeling Safe-NL Programme will be more cost-effective than formulation-based CBTp (from baseline to 18-month follow-up). The trial will also include an explanatory component. We hypothesize that changes in the key maintenance factors (e.g. worry, low self-esteem, anomalous experiences, insomnia, safety-seeking behaviours or defences, and trauma imagery), resilience, and personal recovery will mediate changes in mental wellbeing and persecutory delusions. We will also record all service use, and other relevant health economic data, for the health-economic evaluation.

### Objectives {7}

The primary objective is to test whether the Feeling Safe-NL Programme is more effective in improving mental wellbeing over time than formulation-based CBTp. The overall effect over time (baseline to 18-month follow-up) and the effects at each timepoint will be determined [27].

The secondary objectives are to test whether the Feeling Safe-NL Programme is more effective than formulation-based CBTp over time in (1) reducing the severity of the persecutory delusion, (2) reducing general paranoid ideation, (3) improving patient chosen outcomes of therapy, and (4) improving activity levels. Additionally, we investigate the mediators of improved mental wellbeing and reduced persecutory delusions and whether the Feeling Safe-NL Programme is more cost-effective than formulation-based CBTp.

### Trial design {8}

A pragmatic single-blind superiority randomized controlled trial with two parallel groups. Patients will be randomized (1:1) to the Feeling Safe-NL Programme or formulation-based CBTp. Measurements are conducted at baseline, 6-, 12-, and 18-month follow-up (see Fig. 1). In both arms, people will receive weekly therapy sessions over a period of 6 months. To support the therapies in both arms, optional self-monitoring is available via brief questionnaires of which the outcomes are visualized. This supports the participant and therapist in monitoring change and shared decision-making.

**Fig. 1 Fig1:**
[figure not shown]
Trial flow diagram

## Methods: participants, interventions and outcomes

### Study setting {9}

Participants will be recruited from outpatient services of several large mental health organizations in the Netherlands (Parnassia Groep, Altrecht and GGZ Oost Brabant) that offer care to people with persecutory delusions.

### Eligibility criteria {10}

We will recruit outpatients with persecutory delusions, independent of DSM classification. The inclusion criteria are main persecutory belief held with at least 60% conviction; low mental wellbeing (score ≤ 43 on the Warwick Edinburgh Mental Well-Being Scale [28], determined using clinical cut-off calculation using the Oxford Feeling Safe sample [5]); and age ≥ 16 years. The exclusion criteria are insufficient competence in the Dutch language to participate in research; currently receiving individual therapy or peer counselling with a frequency of at least one session per month; and unable to understand and sign the informed consent form.

### Who will take informed consent? {26a}

A two-step consent procedure will be used that allows identifying those people that could benefit from the target interventions. First, a local trial therapist or care coordinator asks patients with persecutory delusions for written permission to provide their contact details to the trial assessors so they can provide more information about the study. Second, the patient will be contacted by a trial assessor and informed about the study, both verbally and in writing. Patients then receive at least one week to consider participation in the study. If patients decide to participate, they are invited for a face-to-face meeting in which they can ask additional questions about participation, informed consent is obtained, and inclusion and exclusion criteria are assessed. Eligible participants will be seen for the baseline assessment after which they will be randomized to either Feeling Safe-NL or formulation-based CBTp.

### Additional consent provisions for collection and use of participant data and biological specimens {26b}

N/a. No data are collected for which additional consent provisions are required.

## Interventions

### Explanation for the choice of comparators {6b}

We will compare the Feeling Safe-NL Programme to the international guideline psychological intervention formulation-based CBTp [29, 30]. This will allow us to investigate if the Feeling Safe-NL Programme, involving modular CBT and peer counselling, is more effective than the guideline psychological intervention in the long-term.

### Intervention description {11a}

#### The Feeling Safe-NL Programme

Feeling Safe-NL builds on the Feeling Safe Programme [5] with three adaptions. First, Feeling Safe-NL involves close collaboration between therapists and professional peer counsellors. While therapists work on reducing the maintenance factors of persecutory delusions using targeted CBT and supporting patients to relearn safety, professional peer counsellors focus on addressing personal recovery, together promoting mental wellbeing. Second, Feeling Safe-NL includes trauma imagery as a treatable maintenance factor of threat beliefs [23, 24]. Third, Feeling Safe-NL offers the possibility to self-monitor change to promote people’s agency, shared decision-making and motivation [25, 26]. Feeling Safe-NL involves approximately 20 weekly therapy sessions and 10 bi-weekly individual peer counselling meetings. There are also collaborative meetings (patient, peer counsellor, therapist) to evaluate progress and enhance synergy. This is done at least at the start of the program, near the end of each CBT module and at the end of the program.

Following an introductory meeting with both the therapist and peer counsellor, the therapist and peer counsellor assess the maintenance factors and wishes and needs of the person, respectively. Following this assessment, the therapist offers the patient a menu of relevant CBT modules. Typically, three to four modules are completed, based on patient choice. Modules that can be offered are reducing worry, boosting self-confidence, feeling safe alongside hearing voices, improving sleep, letting go of trauma imagery, and learning to be safe enough through behavioural tests for building safety beliefs. Concurrent to the therapy, the peer counsellor and participant work together according to the sponsor model [31]; the peer counsellor supports the participant during the Feeling Safe-NL Programme based on the participants’ wishes and needs, considering possibilities. The participant and peer counselor work together on personal recovery including identifying and using strengths [22]. The dual approach to improving mental wellbeing is presented in Fig. 2.

**Fig. 2 Fig2:**
[figure not shown]
The dual approach to improving mental wellbeing in the Feeling Safe-NL Programme: relearn safety by offering targeted CBT modules while promoting personal recovery through postulated mechanisms of peer counselling [5, 22–24]

#### Formulation-based CBTp

CBTp will follow the guideline formulation-based manual for persecutory delusions in the Netherlands [32], which is an updated version of the British manuals, e.g [33]. including some options for modular CBT interventions (e.g. competitive memory training for increasing self-confidence, CBT for insomnia, and meta-cognitive training for worry) [34–39] and trauma-focused CBT interventions [40] depending on the psychological case-formulation. Influenced by the earlier development studies for Feeling Safe, there is therefore a degree of overlap in therapy content. The formulation-based CBTp manual for persecutory delusions consists of four phases: introduction, formulation and goal setting, intervention and change techniques, and consolidation. The aim is to reduce the negative behavioural and emotional impact of persecutory delusions, to promote more helpful information processing, perspectives, and behavioural coping strategies and to work towards personal therapy goals.

Both therapies will be delivered by therapists with at least an MSc in Clinical Psychology and 100 hours of accredited CBT training. All therapists will be trained in and deliver both interventions (to eliminate therapist effects). Therapists will receive weekly supervision from a clinical psychologist and CBT supervisor. Therapists start seeing participants for the trial after four recorded therapy sessions (two for Feeling Safe-NL and two for formulation-based CBTp) that have been rated and scored ≥ 4 on each relevant item of the Cognitive Therapy Rating Scale-Revised for Psychosis. Professional peer counsellors meet the standards of the Dutch professional competence profile [18, 19] and receive additional training in strengths-based methodologies [41] and promoting experiential knowledge regarding the six empirical maintenance factors being addressed by the Feeling Safe therapy modules. Professional peer counsellors start seeing participants after their written and practical assignments reflect the list of competencies in the professional competence profile.

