### Sample size {14}

The sample size for longitudinal intention-to-treat (ITT) analyses with linear mixed models (LMM) was calculated according to the method presented by Liu and Liang (1997) and based on data from previous RCTs [5, 13–15, 24]. Although an ITT analysis with LMM is robust against moderate attrition, we aim to include an additional 10% to compensate for potential dropout. With alpha = 0.05; beta = 0.2; rho = 0.5; 3 repeated follow-up assessments and 10% drop-out; we will need 95 participants in each arm to detect small to medium effects (0.35). Therefore, we aim to include 190 participants.

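### Having therapists work in both arms does not eliminate provider effects: peer counsellors are nested in one arm, and neither the listed model terms nor the sample size allows for this

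*Protocol article*

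**What the plan says.** Under Intervention description {11a}, in the part on formulation-based CBTp, the protocol article states: "All therapists will be trained in and deliver both interventions (to eliminate therapist effects". The part on the new programme adds a second kind of provider: "Feeling Safe-NL involves approximately 20 weekly therapy sessions and 10 bi-weekly individual peer counselling meetings". The Qualitative interviews section confirms that only Feeling Safe-NL participants have a peer counsellor. Sequence generation {16a} balances allocation by site and does not mention therapists or counsellors.

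Statistical methods {20a} describes a linear mixed model with baseline value, categorical time and condition, plus time-by-condition effects. It names no therapist or counsellor term. Sample size {14} gives its inputs as "With alpha = 0.05; beta = 0.2; rho = 0.5; 3 repeated follow-up assessments and 10% drop-out" and concludes that "we will need 95 participants in each arm to detect small to medium effects (0.35" standard deviations. No provider ICC, caseload or design effect enters. The rho of 0.5 is the correlation between repeated measurements on one patient.

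**The concern.** Provider variation has three components, and crossing therapists with arm deals with only one.

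- **Therapist main effect.** A generally better therapist raises outcomes in both arms, and this largely cancels in the comparison.
- **Therapist-by-treatment variation.** Some therapists do relatively better with one treatment. This does not cancel.
- **Peer-counsellor effect.** Patients who share a counsellor share part of their outcome, in one arm only. This is a partially nested design, and nothing in the control arm can cancel it.

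If the second or third component is present and the analysis treats patients as independent, the standard error of the arm difference is too small and the 5% test rejects too often. If the component is modelled, the standard error is right, but the sample size was not set for it.

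**Working it through.** **1. The plan's own figure.** Inputs from Sample size {14}: alpha 0.05 (sidedness is not stated, but two-sided reproduces the result), power 0.80, rho 0.5, three follow-ups, effect 0.35, drop-out 10%.

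n per arm = 2 × (1.96 + 0.842)² × [(1 + 2 × 0.5)/3] / 0.35² = 85.4, and 85.4/0.9 = 94.9, so 95 per arm. The figure reproduces with independent patients, leaving 95 × 0.9 = 85.5 evaluable per arm.

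**2. Assumptions not in the documents.** 8, 12 or 16 peer counsellors with equal caseloads, so m = 85.5/k patients each; ICC 0.02, 0.05 or 0.10. Two ways of scaling the ICC are shown.

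**3. Scaling A: ICC as a share of the variance of a patient's mean over follow-up.**

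- Design effect in Feeling Safe-NL: DE = 1 + (m − 1) × ICC. Variance inflation of the arm difference: f = (DE + 1)/2.
- Type I error if ignored: 2 × [1 − Φ(1.96/√f)]. Power if modelled: Φ(2.80/√f − 1.96).

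Middle case (12 counsellors, ICC 0.05): m = 7.125; DE = 1 + 6.125 × 0.05 = 1.306; f = 1.153; √f = 1.074. The true standard error is 7% larger than the one used, type I error is 6.8% and power is 74%.

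**4. Scaling B: ICC as a share of the single-timepoint variance, constant over time.** The patient-mean variance is V in CBTp and V + (m − 1) × ICC in Feeling Safe-NL. V = 2/3 in the plan's formula. If the baseline covariate correlates r with each follow-up, V = 2/3 − r², which is 0.417 at r = 0.5 and 0.577 at r = 0.3.

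Middle case, no baseline gain: SE = √[(0.973 + 0.667)/85.5] = 0.1385, against 0.1249 assumed. Type I error is about 8% and power is Φ(0.35/0.1385 − 1.96) = 71%.

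Middle case, r = 0.5: SE = √[(0.723 + 0.417)/85.5] = 0.115, power 86%. At r = 0.3, power is 76%.

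| Scaling | 16 counsellors, ICC 0.02 | 12 counsellors, ICC 0.05 | 8 counsellors, ICC 0.10 |
|---|---|---|---|
| A: type I if ignored / power if modelled | 5.5% / 78% | 6.8% / 74% | 10.8% / 63% |
| B, no baseline gain | 6% / 78% | 8% / 71% | 14% / 57% |
| B, r = 0.5 | 6% / 92% | 9% / 86% | 18% / 67% |
| B, r = 0.3 | 6% / 83% | 8% / 76% | 15% / 60% |

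The two figures in each cell belong to different analyses: the first to a test that ignores counsellors, the second to one that models them. On scaling A, power of the test that ignores them is Φ(0.84/√f), about 78% in the middle case and 76% in the worst.

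**5. Simulation of a test that ignores providers** (20,000 runs per case, 86 per arm, 10 therapists, 9 counsellors, patient-mean variance 2/3, no true difference):

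| Variance component ignored | Type I error |
|---|---|
| None | 4.9% |
| Therapist main effect 0.05, crossed | 4.2% |
| Therapist-by-treatment 0.02 in each arm | 7.6% |
| Counsellor 0.02 | 6.6% |
| Counsellor 0.05 | 8.5% |
| Therapist main effect 0.05 and counsellor 0.05 | 8.0% |

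**The case against.** Several stronger readings are tempting, and the documents do not support them.

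- **That every standard error is too small.** For the therapist main effect, the design is sound. Ignoring a crossed main effect is neutral to conservative (4.2% in simulation), and it slightly offsets counsellor clustering (8.0% against 8.5%).
- **That the 80% power is not delivered.** This needs an ICC and a number of counsellors, and the documents give neither. The sample-size formula also takes no credit for the planned baseline covariate, which at an assumed correlation of 0.5 gives 86% in the middle case. The offset is not certain. Entry is restricted to low WEMWBS scores (43 or less), which tends to weaken that correlation. Nor does it help type I error: with a smaller residual variance and the same counsellor variance, ignored clustering counts for more (8% rises to 9% in the middle case).
- **That the excess false positives favour the new programme.** One-arm clustering does not bias the difference. Under the null, excess rejections fall equally in both directions.
- **That peer counselling is half of the new intervention.** The stated contacts are about 20 therapy sessions and 10 counsellor meetings, so one third of individual contacts, plus joint meetings.
- **That the plan excludes provider effects.** The article names no random effect at all, not even one for patient. The random structure is unspecified, and a statistical analysis plan that is not shown may include provider terms. Their absence from the article is therefore not in itself an error. The printed claim about therapist effects stands regardless, and so does a sample size that assumes independent patients.

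A full provider model is also heavy for about 85 patients per arm. If therapists and counsellors work in the same local pairs, their variances may be hard to separate. That bears on the form of the fix.

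**Conclusion.** The point holds in a limited form. Crossing therapists with arm balances therapist main effects. It does not remove therapist-by-treatment variation, and it does nothing for counsellors nested in Feeling Safe-NL. With only the terms listed, the standard error of the arm difference is too small, and two-sided type I error exceeds 5%, to the extent that either component is above zero.

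The size is conditional on assumed inputs. For 8 to 16 counsellors and ICC 0.02 to 0.10, type I error is about 5.5 to 10.8%, or about 6 to 14% with the ICC on single-timepoint variance and no baseline gain. The 80% power is not assured: 78 to 63% on the plan's own formula once clustering is modelled, with a possible but unquantified offset from the baseline covariate. This should be corrected, but it does not undermine the trial.

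**What to change.** 1. In Intervention description {11a}, limit the claim to balancing therapist main effects between arms.
2. Record therapist and peer-counsellor IDs for every participant.
3. In the primary mixed model, add a peer-counsellor random effect that is active only in the Feeling Safe-NL arm, with Kenward-Roger or Satterthwaite degrees of freedom.
4. Add a therapist-by-condition random effect as a sensitivity analysis, or in the main model where it can be estimated. Pre-specify how the model is simplified if a variance is estimated at zero or the components cannot be separated.
5. In Sample size {14}, state that 95 per arm assumes no provider clustering, and give power over a range of ICCs and caseloads with the assumed baseline correlation.

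The cost is small. The IDs are known from delivery, and since analyses are planned only at the end of the trial, the model can be specified before then. The price is somewhat wider confidence intervals and, if the target of 190 is kept, an open statement that power may be below 80%.
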